## Abstract

**Background:**

Radical cystectomy for bladder cancer is associated with a high risk of needing red blood cell transfusion. Tranexamic acid reduces blood loss during cardiac and orthopedic surgery, but no study has yet evaluated tranexamic acid use during cystectomy.

**Methods:**

A randomized, double-blind (surgeon-, anesthesiologist-, patient-, data-monitor-blinded), placebo-controlled trial of tranexamic acid during cystectomy was initiated in June 2013. Prior to incision, the intervention arm participants receive a 10 mg/kg loading dose of intravenously administered tranexamic acid, followed by a 5 mg/kg/h maintenance infusion. In the control arm, the patient receives an identical volume of normal saline that is indistinguishable from the intervention. The primary outcome is any blood transfusion from the start of surgery up to 30 days post operative. There are no strict criteria to mandate the transfusion of blood products. The decision to transfuse is entirely at the discretion of the treating physicians who are blinded to patient allocation. Physicians are allowed to utilize all resources to make transfusion decisions, including serum hemoglobin concentration and vital signs. To date, 147 patients of a planned 354 have been randomized to the study.

**Discussion:**

This protocol reviews pertinent data relating to blood transfusion during radical cystectomy, highlighting the need to identify methods for reducing blood loss and preventing transfusion in patients receiving radical cystectomy. It explains the clinical rationale for using tranexamic acid to reduce blood loss during cystectomy, and outlines the study methods of our ongoing randomized controlled trial.

**Trial registrations:**

Canadian Institute for Health Research (CIHR) Protocol: MOP-342559; ClinicalTrials.gov, ID: NCT01869413. Registered on 5 June 2013.

**Electronic supplementary material:**

The online version of this article (10.1186/s13063-018-2626-3) contains supplementary material, which is available to authorized users.

## Background

Bladder cancer is the sixth most common cancer in North America with an estimated 80,000 new diagnoses in 2011 [1, 2]. Among incident cancers it is estimated that 8% (6400 per year) will undergo radical cystectomy [3]. Radical cystectomy is an advanced surgical procedure that involves removal of the urinary bladder, adjacent organs, and pelvic lymph nodes. Removal of the urinary bladder also necessitates urinary reconstruction using an isolated segment of small or large intestine for urinary diversion. The extensive extirpative and reconstructive components of this surgery result in prolonged operative times and are associated with significant risk of complications including high risk of perioperative bleeding and subsequent need for blood transfusion [4]. Among individual surgeons at institutions that perform many procedures, median intraoperative blood loss is between 600 and 1700 mL [5–7]. The incidence of at least one intraoperative blood transfusion is 9 to 67% [5–9], and the postoperative transfusion risk is at least 15% [6, 9]. Among cystectomy patients who receive transfusion, a median of 2 units of blood cells are given [6, 9].

Lysine analog drugs are synthetic derivatives of the amino acid lysine that reversibly block lysine-binding sites on plasminogen molecules [10]. This action prevents the conversion of plasminogen to plasmin, the active enzyme that degrades fibrin clots. Therefore, lysine analogs decrease the breakdown of clots and are considered anti-fibrinolytics. There are two commonly studied lysine analogs, tranexamic acid and epsilon-aminocaproic acid. Both of these drugs have been shown to decrease blood transfusion need during some surgeries without a significant increase in adverse events.

In 2011, urologists who specialize in cancer treatment (members of the Society of Urologic Oncology) were surveyed about the methods they used to prevent blood loss during radical cystectomy [11]. Respondents were asked about their use of systematic techniques, systemic drugs, and topical agents to reduce blood loss and prevent blood transfusion. Topical agents were commonly used among expert urologists (73% used oxidized cellulose polymer; 53% used gelatin and thrombin matrix) and 28% used at least one systematic technique such as autologous blood recovery. Systemic drugs, such as lysine analogs, were used by only 5% of surgeons.

The infrequent use of lysine analogs during radical cystectomy may be due to lack of high-quality evidence supporting their effectiveness in this setting. While numerous cardiac and orthopedic surgery studies have evaluated the effect of intraoperative lysine analogs [12], a recent systematic review of major pelvic surgery failed to identify a single cystectomy trial [13].

In summary, radical cystectomy is associated with a high risk of clinically significant blood loss and blood transfusion, while lysine analogs have been shown to decrease these risks during other types of surgery. Therefore, our objective is to determine the effect of lysine analogs during radical cystectomy using a placebo-controlled randomized trial. We chose to use tranexamic acid as the study drug because of its ease of administration, demonstrated benefit in other procedures, safety profile, and familiarity of use in other surgical procedures.

### Objectives and research questions

The primary objective is whether the use of systemic tranexamic acid compared to placebo reduces the proportion of radical cystectomy patients requiring red blood cell transfusion up to 30 days post operative (anticipated 50% transfusion rate with placebo to 35% with tranexamic acid). Secondary objectives are to determine the effect of tranexamic acid on intraoperative blood loss, number of transfused blood products, and post-operative complications. Specifically, thrombotic events will be evaluated.

## Methods

### Study setting and design

This study was initiated at The Ottawa Hospital, a regional cancer referral center in Ottawa, Canada. Thirteen urologic oncology centers in Canada have committed to participate (University of Ottawa, University of Toronto, University of Western Ontario, Université de Montréal, McGill University, Université Laval, Dalhousie University, Queen’s University, McMaster University (Hamilton Health and St. Joseph’s Healthcare), University of Alberta, University of British Columbia, and University of Manitoba). Patients are randomized to receive either tranexamic acid (intervention) or placebo (control).

In keeping with a pragmatic approach to this study, we have adopted permissive eligibility criteria, an easily administered protocol, outcomes that are of relevance to physicians, patients, and health administrators, and limited data collection. Evaluation and flow of patients prior to, during, and following surgery will be according to usual standard of care. The study flowchart is presented in Fig. 1, and the timeline of study/outcome assessments is outlined in Fig. 2.

**Fig. 1 Fig1:**
[figure not shown]
Study flowchart

**Fig. 2 Fig2:**
[figure not shown]
Timeline of study procedures and outcome assessments

### Eligibility criteria

#### Study population

Patients undergoing radical cystectomy for treatment of bladder cancer. In keeping with a pragmatic approach to this study, eligibility criteria are inclusive, allowing for the wide generalizability of results.

#### Inclusion criteria

Consenting adult patients (aged ≥ 18 years) undergoing radical cystectomy for bladder cancer are considered eligible, regardless of tumor stage and histology. Patients who have undergone previous surgery, radiation, or chemotherapy may be included. Extent of lymph node dissection is not prescribed. All forms of urinary diversion (conduit, orthotopic continent, or continent cutaneous) are allowed. Use of perioperative thromboprophylaxis (e.g., anti-coagulants, thromboembolism-deterrent stockings, sequential compression devices) are permitted and are at the discretion of the care providers.

#### Exclusion criteria

Patients are excluded from enrollment if they (1) are unable or unwilling to receive red blood cell products due to medical or personal reasons; (2) are pregnant (confirmed by βHCG test); (3) have a known allergy to tranexamic acid; (4) have acquired disturbances of color vision; (5) have a history of subarachnoid hemorrhage; or (6) have thromboembolic disease (active or diagnosed within 1 year), such as deep vein thrombosis (DVT), pulmonary embolism (PE), or cerebral thrombosis.

### Study interventions

The study intervention is Canadian-sourced tranexamic acid (Cyklokapron® made by Pfizer). Tranexamic acid is administered intravenously at a dose of 10 mg/kg within 10 min (loading dose) prior to the surgical incision, followed by 5 mg/kg/h continuous maintenance infusion for the length of surgery (stopped ± 20 min from skin closure). For example, an 80-kg patient would receive 800 mg prior to incision and a 400 mg/h infusion for the duration of surgery.

#### Description and justification of dose

There is no defined dosing schedule for tranexamic acid administration. A wide range of doses and schedules have been used in clinical trials [12]. In 34 cardiac surgery trials investigating the efficacy of tranexamic acid, the loading dose ranged from 2.5 to 100 mg/kg while the maintenance infusions ranged from 0.25–16 mg/kg/h [12]. In 31 non-cardiac surgery trials investigating the efficacy of tranexamic acid, the majority (27) in orthopedic surgery, loading doses ranged from 10 to 40 mg/kg and maintenance infusions ranged from 1 to 40 mg/kg/h [12]. The most common loading dose from all trials was 10 mg/kg and the most common infusion dose was 10 mg/kg/h in non-cardiac surgery and 1 mg/kg/h in cardiac surgery (not including doses of drug used to prime the bypass machine). Dosing strategies were highly variable as some studies did not use a loading dose while others gave only single or intermittent doses.

The serum half-life of tranexamic acid is 120 min when administered intravenously [14]. Without a loading dose it would take as long as 10 h to reach a steady-state serum concentration when the maximum treatment effect would be observed. Therefore, we decided that a loading dose is essential to ensure adequate drug concentration at the time of the initial incision so that the maximum effect of the drug coincides with the greatest risk for bleeding. Furthermore, given the relatively short half-life of tranexamic acid and the long duration of cystectomy surgery, a maintenance infusion is more likely to maintain therapeutic serum concentrations compared to intermittent bolus dosing.

Given the safety profile of tranexamic acid and the potential dose-related response (in vitro) we believed that it was important to choose a dose large enough to be confident that we are achieving therapeutic drug concentrations. A 10 mg/kg loading dose has been frequently studied and should achieve a therapeutic serum concentration. In addition, the maintenance infusion dose suggested for bypass surgery (5 mg/kg/h) is within the range of studied doses and should be sufficient to maintain drug levels throughout surgery.

#### Pharmacy preparation and administration of tranexamic acid or placebo

Ampoules of tranexamic acid (10 mL) of concentration 100 mg/mL are secured by the pharmacy. Mixtures of tranexamic acid remain stable for up to 24 h when refrigerated; therefore, the local research pharmacist or pharmacy technician accesses the online patient allocation and prepares the study drug or placebo within a 24 h period prior to the anticipated completion of the scheduled cystectomy. All mixtures are kept refrigerated from the time of mixing until time of use unless used immediately. The weight-based dose to administer for each patient is confirmed by the administering anesthesiologist using a weight-based dosing nomogram provided by the coordinating center’s pharmacy research technician. The research site’s pharmacy staff also has access to the patient’s weight and dosing nomogram in order to prepare the study products. Study drugs are stored in a secure, locked location at each site’s pharmacy department. Health Canada regulations mandate monitoring and documenting temperature daily as the medication must be stored at room temperature prior to mixing.

#### Placebo control

As there is no standard of care concerning administration of anti-fibrinolytic agents in cystectomy procedures, controls follow the same dosing and schedule described above, but receive 0.9% sodium chloride only.

Other techniques, agents, or equipment may be used at the discretion of the anesthesiologist/surgeon to prevent blood loss, and are recorded. These may include acute normovolemic hemodilution, autologous blood banking, systemic hemostatics (e.g., factor VIIa), topical agents (e.g., oxidized cellulose), and instruments such as thermal devices (e.g., Ligasure®).

### Study outcomes

#### Primary outcome

The primary outcome of the trial is whether or not the patient was transfused at least 1 unit of packed red blood cells up to 30 days post operative. We will compare the proportion transfused at least 1 unit of packed red blood cells between tranexamic acid and placebo study arms. In keeping with our pragmatic approach and difficulty in defining a transfusion protocol, there are no strict criteria to mandate the transfusion of blood products. The decision to transfuse is entirely at the discretion of the treating physicians who are blinded to patient allocation. Physicians are allowed to utilize all resources to make transfusion decisions, including serum hemoglobin concentration and vital signs.

#### Secondary outcomes

Secondary outcomes will assess other transfusion metrics and perioperative safety, cumulative to 30 days post operative. Documentation includes total units of red blood cells transfused, occurrence of postoperative bleeding requiring intervention (e.g., reoperation or angioinfarction), occurrence of platelet transfusion, total units of platelets transfused, occurrence of plasma transfusion, total units of plasma transfused, estimated intraoperative blood loss, and change in hemoglobin. Safety outcomes include occurrence of severe adverse events, such as DVT, PE, myocardial infarction (MI), and cerebral infarction. We also capture treatment “failures” noted as the need for anti-hemorrhagic rescue interventions such as topical agents (e.g., oxidized cellulose) and recombinant factor VIIa.

#### Sequence and frequency of follow-up

Data is collected prior to surgery, during surgery, at the time of hospital discharge, and at 30 days post operative (Fig. 2). At each data collection time point, a detailed review of the health record is conducted by the site research coordinator. Laboratory tests are drawn as per standard clinical care at each institution. A 30-day post-surgery follow-up for adverse events is conducted through both health records and a 30-day phone interview. If the patient reports re-admission to hospital or outpatient intervention for a complication within 30 days of surgery, the medical record from the outpatient visits is reviewed and abstracted. Case Report Forms (CRFs) are completed at each study time point and are supported fully by source documents (charts, reports, laboratory result sheets).

### Sample size

A patient record review from The Ottawa Hospital indicated that red blood cell transfusions were performed in approximately 60% of patients with bladder cancer undergoing radical cystectomy. However, we anticipate that transfusion rates are likely to decrease slightly while under the study protocol. From the results of our survey, systemic anti-fibrinolytics are rarely used during radical cystectomies; to influence practice we suggest that tranexamic acid will have to produce a substantial reduction in the proportion of patients requiring transfusion. To assist in determining the minimally important effect of tranexamic acid deemed necessary to change clinical practice, Canadian experts in the surgical treatment of bladder cancer were surveyed in February 2012. Minimally important effect sizes ranged from an absolute difference of 15% (relative risk (RR) 30%) to 30% (RR 60%) and are consistent with effects observed in many clinical trials of tranexamic acid [12]. From our systematic review of lysine analogs to prevent bleeding during pelvic surgery, the pooled estimate favored lysine analogs (RR 0.69; 95% confidence interval (CI) 0.47 to 1.00) [13].

If 50% of placebo patients will require at least one transfusion within 30 days of surgery, and if the use of tranexamic acid reduces the need for transfusion within 30 days to 35% of patients (15% absolute reduction), and assuming 80% power to detect this absolute difference, with a two-sided alpha level of 5%, the required sample size is 340 people (170 per treatment group). To account for 2% non-compliance with the protocol (possibly due to intraoperative complications or protocol deviations) the total sample size required was estimated to be 354 patients (177 per arm) [15].

### Recruitment

We are implementing a number of initiatives to maintain recruitment, including regular tracking, monitoring and reporting of recruitment activity at each participating site, regular newsletters, progress reports and regularly scheduled investigator and research staff meetings. Participants have the right to withdraw from the study at any time, but are advised to discuss this decision with the site’s qualified investigator or study coordinator before stopping the study. Information given to the research team before the participant withdraws consent may still be used to analyze the study.

### Allocation of intervention

#### Randomization

Eligible and consenting patients are randomized using computer-generated random numbers before surgery in a 1:1 allocation ratio to one of the two arms of the study using permuted blocks of variable length (2, 4, and 6). Patients are also stratified by center.

### Blinding

#### Blinding of allocation arm

Randomization, centralized allocation management, and permuted blocks of variable length are used to ensure that participating centers and physicians remain unaware of the randomization sequence. The pharmacy research staff have exclusive access to their site’s randomization schedule and are expressly forbidden to discuss individual treatment allocation with the study team, the patient, the operating room and clinical care team unless emergency un-blinding is requested and approved by the principle investigator.

#### Blinding of intervention

Tranexamic acid, diluted in saline or undiluted, is clear, colorless, and indistinguishable from saline both at rest and when vigorously agitated [16]. Matching placebo maintenance infusions are identical saline bags without discarded saline or added drug in order to maintain the same volume and weight. To minimize sources of selection and ascertainment biases, anesthesiologists, surgeons, investigators, research staff, and members of the Data Safety and Monitoring Board (DSMB) are all blinded to randomization schemes and treatments administered; only the statistician has access to randomization schemes. The research pharmacist does not have contact with the study team or the patient, and is expressly forbidden to discuss individual treatment allocation with the operating room and clinical care team (a signed confidentiality agreement is obtained from each site research pharmacy personnel). Clinical teams are permitted to unmask treatment allocation only under exceptional circumstances. A request to unmask allocation for an individual patient is made to the coordinating center. A clinical member of the Executive Committee (24 h availability) reviews the request to ensure that it is necessary, based on pre-established criteria.

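### As written, only the active maintenance bags are manipulated, and the stated matching covers contents, volume and weight but not the handling or appearance of the container

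*Protocol article*

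**What the plan says.** All references are to the protocol article.

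- **Placebo maintenance bag** (Blinding of intervention): "Matching placebo maintenance infusions are identical saline bags without discarded saline or added drug in order to maintain the same volume and weight".
- **Look of the fluid** (same section): tranexamic acid, diluted or not, "is clear, colorless, and indistinguishable from saline both at rest and when vigorously agitated".
- **Claimed result** (Abstract, Methods): in the control arm "the patient receives an identical volume of normal saline that is indistinguishable from the intervention".
- **Source of the drug** (Pharmacy preparation and administration of tranexamic acid or placebo): "Ampoules of tranexamic acid (10 mL) of concentration 100 mg/mL are secured by the pharmacy". The pharmacist or technician "accesses the online patient allocation and prepares the study drug or placebo within a 24 h period" before the expected end of surgery.
- **Who receives the product** (same section): the dose is "confirmed by the administering anesthesiologist using a weight-based dosing nomogram". Blinding of intervention lists anesthesiologists and surgeons among those who are blinded.
- **Primary outcome** (Primary outcome): no strict transfusion criteria apply, and "The decision to transfuse is entirely at the discretion of the treating physicians who are blinded to patient allocation".

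**The concern.** Stating that placebo bags have no saline discarded and no drug added has a purpose only if active bags have both. The article therefore describes unequal handling by arm, and the reason it gives is equal volume and weight. Entering a bag to withdraw fluid and add drug can leave signs on the container that equal volume, equal weight and a clear solution do not hide. The article does not list the container among the matched features.

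The design leans on the blind more than most. With no transfusion trigger, blinding is the main safeguard against a decision colored by knowledge of the arm. Other outcomes are exposed too. The Placebo control section leaves additional blood-sparing measures to the anesthesiologist or surgeon. Secondary outcomes include estimated blood loss, and the need for hemostatic rescue is counted as treatment failure. A cue tied to preparation would point the same way in every patient, so a larger sample would not average it out.

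**Working it through.** **1. What is matched and what is not**

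| Feature | Active bag | Placebo bag | Matched in the text? |
|---|---|---|---|
| Look of the fluid | clear, colorless | clear, colorless | yes |
| Volume and weight | saline out, drug in (implied) | unchanged | yes |
| Withdrawal and addition | done (implied) | stated as not done | no |
| Ports, seals, covers, labels | not described | not described | not addressed |

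The third row is the finding. The fourth is silence, which an article may leave to a pharmacy manual.

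**2. Is the exchange more than nominal?** Study interventions gives a maintenance rate of 400 mg/h for an 80-kg patient, and the ampoules hold 100 mg/mL. Drug volume = 400 × hours / 100 = 4 mL per hour of infusion. The article gives no duration of surgery, so 4, 6 and 8 h are assumed, giving 16, 24 and 32 mL. Active bags thus need a real exchange.

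**3. The plan's own sample size.** Inputs from the Sample size section: 50% against 35%, two-sided 5% level, 80% power. With pooled variance under the null and no continuity correction:

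n = [1.96 √(2 × 0.425 × 0.575) + 0.8416 √(0.50 × 0.50 + 0.35 × 0.65)]² / 0.15² = (1.370 + 0.582)² / 0.0225 ≈ 169.3, so 170 per arm and 340 in total, as stated. Then 340 / 0.98² = 354.02, which agrees with the stated 354 (177 per arm). The point here does not question this figure; 177 per arm is carried forward.

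**4. Illustration of what a spurious difference would do.** The documents give no figure for such a bias, so it is assumed. Let there be no true drug effect, 50% transfused on placebo, 50% − b on active, and n = 177 per arm.

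- p̄ = average of the two rates
- SE₀ = √(2 p̄(1 − p̄)/n)
- SE₁ = √([p₁(1 − p₁) + p₂(1 − p₂)]/n)
- Rejection rate = Φ((b − 1.96 SE₀)/SE₁) + Φ((−b − 1.96 SE₀)/SE₁)

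For b = 0.02: SE₀ = √(2 × 0.49 × 0.51/177) = 0.05314 and SE₁ = √((0.25 + 0.2496)/177) = 0.05313. The rate is Φ(−1.584) + Φ(−2.337) = 0.0566 + 0.0097 = 0.066.

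| Assumed spurious difference | Two-sided error (nominal 5%) |
|---|---|
| 0 points | 5.0% |
| 2 points | 6.6% |
| 4 points | 11.7% |
| 5 points | 15.6% |

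One way to reach these values is to suppose that the arm is recognized in a fraction f of patients and that this moves transfusion by s points in the drug's favor in each arm, so b = 2fs. With f = 20% and s = 5 points, b = 2 points; with f = 20% and s = 10 points, b = 4 points. Both f and s are assumptions with no source in the article.

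**The case against.** The strongest reply is that nothing shows the blind to be broken. A reader might infer that placebo bags arrive as unopened stock bags, that a punctured port gives the arm away, or that the bags differ visibly in front of the anesthesiologist. The article supports none of these. It does not call the placebo bag unopened, and the pharmacy section says that placebo, too, is prepared. It mentions no ports, seals, overwraps or labels for either arm. Such details usually sit in a pharmacy manual, and their absence from a journal article is not an error.

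The route to bias also needs several undocumented steps: the sign is visible, nothing covers it, the observer knows what it means, and it changes a transfusion decision. The article does not say who hangs the bag. It does not name the anesthesiologist as a transfusion decision-maker, although treating physicians plausibly include that role during surgery. The outcome window runs to 30 days, and the Background gives a postoperative transfusion risk of at least 15%; staff who never saw the bag may make those later decisions. The sentence also concerns maintenance bags only, so nothing follows for the loading dose.

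All of this stands, and it limits the point to a conditional one. The reply does not remove the difference in handling, because the article itself states what is not done to the placebo bag.

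**Conclusion.** The point holds in limited form. The article describes a preparation step that differs by arm and bases its claim of matching on contents, volume and weight. Whether any sign of the difference reaches theatre is unknown, so this is a weakness in the described procedure and not a demonstrated failure of blinding. Its importance rests on two conditions: that handling leaves a visible sign which nothing masks, and that someone who recognizes it influences transfusion or another judged outcome. The size of any bias cannot be derived from the article. The rise from 5% to about 6.6% at 2 points shows only that a small systematic shift would matter against a design difference of 15 points. The change is worth making because it is cheap and because discretionary transfusion leaves the blind as the main protection.

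**What to change.** Change the preparation step so that both arms are handled alike, in one of two ways:

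- withdraw from each placebo maintenance bag the volume that would be withdrawn from an active bag, and replace it with an equal volume of 0.9% sodium chloride; or
- apply identical opaque port covers and blinded study labels to the bags in both arms.

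Volume and weight remain matched, and placebo patients still receive saline only. If the pharmacy manual already provides for this, no change of practice is needed and the sentence under Blinding of intervention should be corrected to say so.

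The cost is a few minutes of pharmacy time, a revised pharmacy instruction and, with the first option, one additional bag entry per placebo patient. The change would still be useful: the article reports 147 of 354 patients randomized, leaving 354 − 147 = 207, and five of the 13 sites not yet set up.
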